**Figure 3 F3:**
[figure not shown]
Structure of ERT for all three parts. After the baseline (crosshair), the emotional stimuli will be presented followed by an interstimulus interval and the emotion recognition question. Part **(a)** shows videos of one person expressing a basic or complex emotion; **(b)** presents two or more people engaging in an emotional social scene; **(c)** consists of morphing videos.

**Pre-stimulation task:** Prior to each stimulation session, the participants will be measured on accuracy of performance and response time on the ERT. This pre-stimulation task without tDCS functions as a reference to compare with the intra-stimulation task, which is presented during tDCS. This comparison will provide information about the acute effects of tDCS on emotion recognition abilities.

**Intra-stimulation training:** During the 20 min of active or sham tDCS, all participants will undergo a structured training that aims to further stimulate the engagement of the targeted circuits during the active and sham tDCS sessions. At the first 5 min of the stimulation, the child-friendly movie *Inside Out* (112), which focuses on emotions and was developed with scientific consultants studying emotions, will be presented. The movie will be interrupted various times to ask questions about the mental state and emotions of the characters. Next, the ERT will be completed by the participants to further stimulate the engagement of the targeted circuits. Afterwards, the next part of the movie, again interrupted with questions, will be presented. This approach will ensure that all participants will be dealing with the same material and therefore are assumed to engage similar brain regions during the stimulation. Furthermore, this repeated examination of emotion recognition performance with the ERT will provide important information about learning curves and session-by-session changes, which may reveal insights into the optimal number of stimulation sessions.

#### Neurophysiological Measures

**EEG data acquisition:** EEG data will be collected from 19 cortical sites (Fp1, Fp2, F3, F4, F7, F8, Fz, FCz, C3, C4, Cz, T5, T6, P3, P4, Pz, O1, O2, and Oz) positioned according to the international 10-20 system using Ag/AgCl electrodes and the Thera Prax Q-EEG System (NeuroConn, Illmenau, Germany). Electrode-skin impedance will be kept below 3 kΩ.

**Resting-state EEG:** Neural oscillations will be recorded in eight 1-min trials, four with eyes-closed (C) and four with eyes-open (O). A guideline-based counterbalanced order (COCO-pause-OCOC) will be used considering disorder-specific characteristics such as a discomfort with longer eyes-closed intervals and minimizing the risk of participants falling asleep in the eyes-closed condition (113, 114).

**MRI data acquisition:** Functional and structural whole-brain imaging will be conducted using a 3-T Siemens MAGNETOM Prisma MR Scanner (Siemens, Erlangen, Germany) equipped with a 64-channel head coil.

**Resting-state fMRI:** RS data will be acquired for 7 min using an echo-planar imaging sequence with the following parameters: TE/TR = 35/728 ms, field of view (FoV) = 192 × 192 × 144 mm, matrix size = 96 × 96, 72 slices, multiband factor = 8, resulting in an isotropic voxel size of 2 mm, flip angle = 55° (optimized Ernst angle), and bandwidth = 3,365 Hz/Px [sequence optimized according to (115)]. To reduce head motion and participant drowsiness, the movie *Inscapes* (116) will be shown during resting-state recordings. This non-social movie features abstract shapes and was developed for the use with children and clinical populations to increase compliance while minimizing cognitive demand (116).

**ToM-task: frith-happé animations (FHA):** To investigate changes in the ability to infer people's thoughts and feelings, a validated ToM-task, the FHA, will be used (117–119). Participants will be instructed to categorize 12 video clips depicting two animated triangles as showing either no interaction/random movements, physical interaction/goal-directed behavior, or emotional interaction/ToM after each video. Additionally, after the four ToM trials only, they need to state how each of the triangles felt at the end of the video using visual analog scales (VAS). VAS are used instead of the original good/neutral/bad decision to allow for more fine-grained inferences. For each decision (i.e., the video category and emotional state of each triangle), subjects are given 5 s, before the paradigm continues, even when no answer was given. One trial contains up to three baseline (BL) periods: (1) Before the videos, BLs are uniformly jittered between 7 and 13 s. (2) Before the category choice, the BL is between 2 and 4 s. (3) In case a ToM video was shown, the BL before the VAS is 6 s minus the duration for 2.

**Emotion recognition task:** Parts (a) and (c) of the ERT (see Figure 3) will be presented during MRI using a jittered and randomized baseline duration between (a) 9–15 s and (c) 5–10 s. Imaging is conducted using the same parameters as for the resting-state recordings.

**Structural MRI:** These measures will be performed to exclude previously unknown alterations in brain anatomy using the following parameters: T1: TE/TR/TI = 2.29/2,300/900 ms, FoV = 165.44 × 240 × 240 mm, matrix size = 256 × 256, 176 slices, 0.94 × 0.94 × 0.94 mm voxel size (rounded), flip angle = 8°, bandwidth = 200 Hz/Px; T2: TE/TR = 408/3,200 ms, FoV = 172.8 × 230 × 230 mm, matrix size = 256 × 256, 192 slices, 0.9 × 0.9 × 0.9 mm voxel size (rounded), flip angle = 120°, bandwidth = 725 Hz/Px. During the structural scans, cartoons will be shown to the participants.

### Outcomes

The primary outcome will be a reduction in ASD symptoms from baseline in the experimental group compared to the sham group. ASD symptoms will be quantified by the raw score of the German version of the SRS (83) assessed by the primary caregiver.

The secondary outcomes will be increased social cognition and emotion recognition quantified by the raw scores of the MASC (105) as well as correct classifications in the ERT and the FEFA 2 (120). Regarding gaze behavior, longer fixation duration on the eyes and increased pupil dilation will be the outcomes on the MASC and ERT. Outcomes on participants and caregiver ratings will be a decrease in ASD symptoms measured with the ATEC (95) and SCQ (96) and an increase in empathy and emotion regulation abilities measured with the ERQ (97), IECA (98), BES (99), GEM (100), and ERC (101). Neurophysiological activity will be measured at baseline and after the intervention using resting-state EEG and fMRI to measure changes in functional connectivity and electrical activity in the brain. We expect an increased resting-state alpha-power, a decrease in the other frequency bands, and an increased connectivity within the ToM network and DMN. An increased regional activation in key areas of the SBN will be the outcomes during the FHA and ERT.

The exploratory outcomes will include participant and caregiver ratings on comorbid symptoms of ASD using the DISYPS III (102). The brain activation in regions involved in emotion recognition processes and cognitive empathy during emotion recognition with the ERT during fMRI will also be examined exploratorily.

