**Emotion recognition task (ERT):** This self-developed task uses videos of faces and social scenes depicting different emotional states to investigate emotion recognition skills. The task involves three parts (see Figure 3 for a graphical illustration) addressing different emotion recognition competencies: (a) shows videos of one person expressing a basic or complex emotion; (b) is more challenging and presents a more naturalistic scenario in which two or more people engage in an emotional and dynamic social scene; (c) consists of morphing videos (displaying a face transitioning from a neutral expression to a basic emotion) and participants will be instructed to interrupt the morphing process as soon as they recognize the displayed emotion. Afterwards, participants will be asked to classify the emotion that was displayed in the video. The emotional stimuli represent all age groups and genders equally and are taken from validated databases. Parts (a) and (b) use stimuli form the EU Emotion Stimuli Set (108, 109), while part (c) uses stimuli from the FACES Database (110, 111). This task was implemented in Python (version 3.6.7) using the PyQt (version 5.15.2) graphics library. The ERT will be employed in pre- and post-measurements to examine changes in correct classifications and response times and to investigate pre–post changes in gaze behavior using the Tobii Pro eye-tracker (Tobii Group, Danderyd, Schweden).

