### Statistical Analysis

For the statistical analyses, repeated measures analysis of variance (ANOVA) and hierarchical linear models (HLMs) will be used. A 4 × 2 mixed ANOVA (primary outcome as dependent variable) with *Time* (pre vs. post vs. follow-up 1 vs. follow-up 2) as the within-subjects factor and *Group* (experimental vs. control group) as the between-subject factor will be conducted to investigate an interaction between time and group. In order to test specific effects, *post-hoc* tests will be employed. A HLM will be formulated to investigate time-dependent changes and group differences in task performance across stimulation sessions. A *p* < 0.05 will be considered statistically significant. Analysis will be conducted in *R* (121).

For the eye-tracking data, analysis of fixation duration and pupil dilation will be done in Tobii Studio 3.4.5 (107) following the preprocessing pipeline of other studies using eye-tracking to investigate emotion recognition and social cognition in adolescents with ASD [for the ERT (17) and for the MASC (106)]. These results in a fixation duration on the specified area of interest (AOI) and a measure of average pupil dilation per video. Further analysis regarding pre–post comparisons of AOIs and pupil dilation will be done in *R* (121) using linear models.

For the EEG data, we will employ the *MNE* library (122) written in *Python* (123) to execute data pre-processing, segmentation, and frequency and connectivity analyses. The raw EEG data of each participant will be segmented into epochs of 2 s. A multi-taper method with adaptive weights will be applied to each epoch to obtain power spectral density (PSD) values in each frequency band of interest. Frequency bands of interest will be delta (0.5–4 Hz), theta (4–8 Hz), and alpha (8–12 Hz). Subsequently, PSD values in each frequency band will be averaged across epochs separately for each participant, measurement occasion, and experimental condition.

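### In the self-stopped morphing part of the ERT, viewing time is itself a response, so eye-fixation duration and correct classifications can move against, or without, a real change in ability

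*Protocol article*

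**What the plan says.** The ERT has three parts. Under Behavioral Tests, part (c) is described as morphing videos, each "displaying a face transitioning from a neutral expression to a basic emotion". For this part "participants will be instructed to interrupt the morphing process as soon as they recognize the displayed emotion". The answer is given later: "Afterwards, participants will be asked to classify the emotion that was displayed in the video". The Figure 3 caption gives the order within a trial: "the emotional stimuli will be presented followed by an interstimulus interval and the emotion recognition question".

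Under Outcomes, the secondary performance outcome is "correct classifications in the ERT and the FEFA 2", and for gaze "longer fixation duration on the eyes and increased pupil dilation will be the outcomes on the MASC and ERT". Neither statement treats part (c) differently from parts (a) and (b).

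Under Statistical Analysis, the eye-tracking processing follows pipelines of cited studies, one of them specific to the ERT. The result is given as "a fixation duration on the specified area of interest (AOI) and a measure of average pupil dilation per video".

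Response times are collected. Behavioral Tests says that their pre-post change will be examined next to correct classifications, but Outcomes does not list them for the ERT. The only model in which the article explicitly places the reaction time of the morphing part is the subject-level fMRI model.

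**The concern.** A fixation duration is comparable between people and visits when everyone sees the stimulus for the same time. In part (c) the participant sets that time, and he sets it by the very skill that the intervention is meant to improve. A boy who recognises emotions sooner has less time in which to look at the eyes. The article counts longer as better, so two intended benefits, faster recognition and more attention to the eyes, pull one score in opposite directions.

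Accuracy has a related problem. A later stop shows a fuller expression and makes the item easier. A boy who becomes more cautious can score more correct answers without recognising emotions any better, and one who stops earlier at equal accuracy has improved without any change in the listed outcome. Average pupil dilation per video is likewise taken over a period whose length and emotional content depend on the stop.

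Randomisation and the sham control do not remove this. Stopping time arises after randomisation, and an effect of stimulation on it would differ between the arms.

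**Working it through.** The plan states no figure on this point, so there is none to reproduce. The structure comes from Behavioral Tests, Outcomes and Statistical Analysis. The article gives no morph length, share of gaze on the eyes, or accuracy curve, so **every numerical input below is an assumption** that serves only to show direction and order of size.

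**1. Gaze: break-even.** Let T be viewing time and s the share of it spent on the eyes. Fixation duration is D = s × T. If T shortens by a fraction x, D stays level only if s is multiplied by 1/(1 − x).

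| Viewing time shorter by | Factor for s | Relative rise needed |
|---|---|---|
| 10% | 1/0.9 = 1.11 | 11% |
| 20% | 1/0.8 = 1.25 | 25% |
| 30% | 1/0.7 = 1.43 | 43% |

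**2. Gaze: examples, starting from s = 30% and T = 5 s, so D = 1.50 s.**

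- Faster, same share: 0.30 × 4 s = 1.20 s, a fall of 20%.
- Faster, higher share: 0.35 × 4 s = 1.40 s, a fall although both features improved. As a share, the same change is +5 percentage points.
- Slightly faster, higher share: 0.35 × 4.5 s = 1.575 s, a rise. The reversal is therefore not inevitable.

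**3. Accuracy.** Assume six response options, and P(correct) = 1/6 + (5/6) × logistic((morph level at stop − threshold)/0.12), where a lower threshold means better skill.

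- Skill fixed (threshold 50%), stops at 50%, 60%, 70% and 80%: 58%, 75%, 87% and 94% correct. Caution alone raises the score.
- Better skill (threshold 40%), stops at 40% or 35%: 58% or 50% correct, against 58% for the less skilled boy who stops at 50%. A real gain shows as no change or a loss.

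**4. Dilution by pooling.** Give parts (a), (b) and (c) equal weight and equal baseline durations, and let only part (c) shorten, by 20%.

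- Share unchanged: (1 + 1 + 0.80)/3 − 1 = −6.7% overall.
- Share up 10%: part (c) is 0.80 × 1.10 = 0.88, a fall of 12%. Overall, (1.10 + 1.10 + 0.88)/3 − 1 = +2.7%.

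Pooling can thus hide the reversal in part (c) or carry a smaller one into the total.

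**The case against.** Several objections have force.

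- **The cited pipeline may already normalise.** It is not shown, and such detail can properly sit in the full protocol or analysis plan. This cannot be excluded. What the article itself states, however, is a fixation duration as the result and longer as the favourable direction.
- **The face may stay on screen.** The text says that the morph is interrupted, not that the image disappears. The caption's sequence of stimulus, interval and question favours the reading that viewing ends at the stop, but this is an inference. If the stopped frame stayed up, viewing time would not simply follow stopping time.
- **Speed is not ignored.** Response times are examined pre and post, and task performance across sessions is to be modelled with a hierarchical linear model. A reader might infer that the plan would lose a gain in speed altogether. The documents do not support that. What remains is that response time is not among the listed ERT outcomes and is not tied to accuracy or gaze.
- **Shared caution cancels.** Both arms get the same instruction and the same training, so common practice effects do not bias the comparison. Only a shift that differs between arms matters, and nothing in the article shows that stimulation causes one. For the gaze measure, though, faster recognition under active stimulation is enough, and that is a plausible form of the intended benefit.
- **The scope is narrow.** Parts (a) and (b), the MASC and the FEFA II are not described as self-stopped. The article calls its secondary outcomes underpowered, and the primary outcome, the caregiver-rated SRS, is untouched.

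**Conclusion.** The point holds in a limited form. As written, the part (c) gaze score falls when recognition speeds up at an unchanged eye share. It can fall even when the share rises, unless the rise reaches 11%, 25% or 43% for viewing times shorter by 10%, 20% or 30%. Correct classifications in part (c) can move with response caution rather than ability.

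This rests on three conditions: that viewing of the face ends at the stop, that the unseen pipeline does not scale to viewing time, and that treatment changes stopping time. The percentages are arithmetic; the example times, shares and accuracy curve are assumed.

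A reader might go further and infer that faster recognition must show as worse gaze, or that the trial would read a real benefit as harm. The documents support neither. Reversal depends on how far the eye share changes, only one of three ERT parts is affected, pooling dilutes the effect, and the other outcomes, including the primary, do not depend on it. It is a weakness in how a secondary outcome is defined, worth correcting because the correction is nearly free.

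**What to change.** For ERT part (c) only:

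- Define the gaze outcome as the proportion of valid viewing time spent on the eyes. If the cited pipeline already does this, say so in one sentence.
- Define performance as stop time or morph level over all trials, reported alongside accuracy. Restricting stop level to correctly classified trials would condition on a result that treatment can itself affect.
- Interpret pupil dilation with viewing time taken into account. A fixed early window is not an obvious remedy, because it would sample near-neutral faces.
- Report part (c) separately. Parts (a) and (b) keep fixation duration and correct classifications.

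Response times and gaze are already recorded, so this needs new wording and no new data. Trial Status describes data collection as ongoing; settling the definition before the analysis avoids a choice of metric after the results are known. The cost is that part (c) no longer contributes to a single ERT score and is reported on its own.

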## Abstract

**Background:** Social–emotional difficulties are a core symptom of autism spectrum disorder (ASD). Accordingly, individuals with ASD have problems with social cognition such as recognizing emotions from other peoples' faces. Various results from functional magnetic resonance imaging and electroencephalography studies as well as eye-tracking data reveal a neurophysiological basis of these deficits by linking them to abnormal brain activity. Thus, an intervention targeting the neural origin of ASD impairments seems warranted. A safe method able to influence neural activity is transcranial direct current stimulation (tDCS). This non-invasive brain stimulation method has already demonstrated promising results in several neuropsychiatric disorders in adults and children. The aim of this project is to investigate the effects of tDCS on ASD symptoms and their neural correlates in children and adolescents with ASD.

**Method:** This study is designed as a double-blind, randomized, and sham-controlled trial with a target sample size of 20 male participants (aged 12–17 years) diagnosed with ASD. Before randomization, the participants will be stratified into comorbid depression, comorbid ADHS/conduct disorder, or no-comorbidity groups. The intervention phase comprises 10 sessions of anodal or sham tDCS applied over the left prefrontal cortex within 2 consecutive weeks. To engage the targeted brain regions, participants will perform a social cognition training during the stimulation. TDCS-induced effects on ASD symptoms and involved neural circuits will be investigated through psychological, neurophysiological, imaging, and behavioral data at pre- and post-measurements. Tolerability will be evaluated using a standardized questionnaire. Follow-up assessments 1 and 6 months after the intervention will examine long-lasting effects.

**Discussion:** The results of this study will provide insights into the changeability of social impairments in ASD by investigating social and emotional abilities on different modalities following repeated sessions of anodal tDCS with an intra-simulation training. Furthermore, this trial will elucidate the tolerability and the potential of tDCS as a new treatment approach for ASD in adolescents.

**Clinical Trial Registration:** The study is ongoing and has been registered in the German Registry of Clinical Trials (DRKS00017505) on 02/07/2019.

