#### Randomization

A total of 20 male participants will be included. To balance the experimental and control group with respect to comorbidities, all participants will be stratified into one of three subgroups based on their clinical presentation: subgroup A for participants without comorbidity, subgroup B for participants with depression as primary comorbidity, and subgroup C for participants with ADHD and/or conduct disorder as primary comorbidity. After subgroup stratification, the participants will be randomly allocated to the active condition or the sham condition by assigning a code to each participant. To ensure a quick study start for the participants after enrollment, a block randomization design will be used.

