#### Safety and Adverse Events

As for potential risks of tDCS, guidelines report no serious adverse events in over 18,000 sessions of low-intensity transcranial electrical stimulation in pediatric and adult patients, as well as in healthy subjects (89). Current data also specifically emphasize the feasibility, tolerability, and safety of tDCS in children and adolescents (45, 63, 90). Adverse effects of tDCS in children and adolescents were described as mild and transient, including tingling (11.5%), itching (5.8%), redness (4.7%), and scalp discomfort (3.1%) (91). Thus, when guidelines are followed, tDCS is a safe modality for children and adolescents with various neurological conditions (92). The proposed parameters of this study (including electrode size, current strength, and duration) were previously tested for their safety in children younger than the participants in this study (93, 94). The brain stimulation device will be operated by experienced psychologists, neuroscientists, and research assistants trained in the application. Therefore, no serious adverse events or serious health risks for the participants of this study are expected. In the case of a serious adverse event, the participant will be excluded from the trial and the adverse event will be reported to the ethics committee of the Medical University of Vienna and to the Austrian Agency for Health and Food Safety (AGES). To protocol adverse effects, the German version of the questionnaire of sensations related to transcranial electrical stimulation will be used at the last stimulation session (accessible at: http://neurologie.uni-goettingen.de/downloads.html).

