### Instruments

In accordance with the complexity of the disorder, the effects of the tDCS intervention will be investigated at three different levels:

Psychological ratings to detect changes in ASD symptoms as well as in comorbid symptoms;Neurophysiological measures to detect changes in brain responses to emotional stimuli;Behavioral tests to detect changes in responses and gaze behavior.

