#### Psychological Ratings

Clinical information *via* questionnaires will be collected from participants and caregivers following a multi-perspective approach. The Social Responsiveness Scale [SRS; (83)] reliably indicates the presence and severity of social impairment in ASD and correlates with real-world dysfunctional behaviors. Five subscales (social awareness, social cognition, social communication, social motivation, restricted interests and repetitive behavior) and a total score will be calculated. Additionally, various instruments targeting different aspects of ASD symptoms [Autism Treatment Evaluation Checklist—ATEC (95); Social Communication Questionnaire—SCQ (96)] will be used for pre-, post-, and follow-up assessments. Furthermore, affective and cognitive components of empathy and emotion regulation abilities will be measured *via* self-reports [Emotion Regulation Questionnaire—ERQ (97); Index of Empathy for Children and Adolescents—IECA (98); Basic Empathy Scale—BES (99)] and parental questionnaires [Griffith Empathy Measure—GEM (100); Emotion Regulation Checklist—ERC (101)]. For subgroup stratification and the investigation of comorbid symptoms of ASD such as attention deficit, anxiety, aggression, and depression, the Diagnostic System for Mental Disorders in Childhood and Adolescence for ADHD, Depression, Anxiety, and Conduct Disorder [DISYPS III ADHS, DEP, ANG, SSV—self- and parental rating versions; (102)] will be used.

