In conclusion, children and adolescents with ASD are in need of an effective treatment, and modulating brain activity could be a first step toward a new efficient intervention. This neurophysiologically based approach benefits from being non-invasive, being easy to administer, and having only mild and transient side effects (92, 138). TDCS further aims to overcome shortcomings of traditional interventions, such as often long and expensive treatment periods (5). Taken together, this study will provide information about the efficacy of tDCS and the potential to establish it as an affordable alternative or additive treatment for individuals with ASD in the long run.

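### Non-serious psychiatric worsening, and non-serious effects after session 10, lie outside the prespecified tolerability assessment, although the trial already has an instrument that could describe the former

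*Protocol article*

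**What the plan says.** The Abstract promises that "Tolerability will be evaluated using a standardized questionnaire" and that the trial will throw light on how well adolescents with ASD tolerate tDCS. The section Safety and Adverse Events names the instrument and its single timepoint: "To protocol adverse effects, the German version of the questionnaire of sensations related to transcranial electrical stimulation will be used at the last stimulation session". The Discussion names the same questionnaire as the means of monitoring how participants react to the stimulation.

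That section also provides for serious events: "In the case of a serious adverse event, the participant will be excluded from the trial and the adverse event will be reported", the recipients being the ethics committee and the Austrian agency.

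The DISYPS III, in self- and parent-rated versions, is introduced under Psychological Ratings for stratification and for studying "comorbid symptoms of ASD such as attention deficit, anxiety, aggression, and depression". Instruments describes the purpose of this group of measures as "Psychological ratings to detect changes in ASD symptoms as well as in comorbid symptoms". Outcomes then fixes its status: "The exploratory outcomes will include participant and caregiver ratings on comorbid symptoms of ASD using the DISYPS III".

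Under Randomization, one stratum holds participants without comorbidity. The other two are "subgroup B for participants with depression as primary comorbidity, and subgroup C for participants with ADHD and/or conduct disorder as primary comorbidity". Exclusion Criteria rules out concomitant psychopharmacological medication. The Figure 1 caption places post-treatment measures in the week after the sessions and follow-ups at 1 month and 6 months.

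**The concern.** The article chooses one instrument and one moment for tolerability. By its title, the instrument asks about sensations from the stimulation. It is given at session 10, before the post visit and both follow-ups.

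The trial stimulates the prefrontal cortex of adolescents, some enrolled with depression or with ADHD/conduct disorder as primary comorbidity. It follows clinical symptoms for 6 months because effects might persist. If a benefit may outlast stimulation, an unwanted change in mood or behaviour may do so too. A participant whose depression or aggression rating rises without reaching the threshold of a serious event would not enter the tolerability assessment as described. Nor would a non-serious complaint that begins after session 10.

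What is at stake is the scope of one conclusion. A report of good tolerability could be read as covering mood and behaviour when the assessment behind it covers sensations on one day. The primary analysis of the SRS is not affected.

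**Working it through.** The article gives no figure for this point, so there is none to reproduce. The check sets the sections side by side and then asks what the sample can show.

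**1. Which kinds of harm have a stated route**

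| Kind of harm | Stated route | Source |
|---|---|---|
| Stimulation sensations | Questionnaire, final session | Abstract; Safety and Adverse Events; Discussion |
| Serious event, any type, any time | Exclusion and report to two bodies | Safety and Adverse Events |
| General well-being during the two weeks | Brief questionnaire before each session, not called a safety measure | Intervention |
| Non-serious worsening of depression, anxiety or aggression | DISYPS III, exploratory outcome, no safety role | Psychological Ratings; Outcomes |
| Non-serious effects after session 10 | None stated as part of tolerability | – |

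The last two rows are the gap.

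**2. Length of the later period**

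Ten sessions take 2 weeks. The last visit is 6 months, about 26 weeks, later. The total is 2 + 26 = 28 weeks, so about 26/28 = 93% of the observation time follows the only tolerability assessment. The serious-event route is not confined to the first 2 weeks, so this share applies to non-serious effects only.

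**3. What the sample can show**

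The article gives 20 participants but no allocation ratio. I assume 10 per arm.

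- Zero cases in 10: the one-sided 95% upper limit is 1 − 0.05^(1/10) = 25.9%. The upper end of the two-sided 95% interval is 1 − 0.025^(1/10) = 30.8%.
- Chance of seeing at least one case in 10 at true rate p is 1 − (1 − p)^10: 9.6% for p = 1%, 40.1% for p = 5%, and 65.1% for p = 10%.

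Even complete collection would therefore neither exclude a substantial rate of worsening nor support a test between arms. It supports a listing of individuals with wide intervals.

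**4. When the DISYPS III is collected**

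The text gives no visits for this instrument. The pre-, post- and follow-up schedule under Psychological Ratings stands in the sentence on the ATEC and SCQ, and Figure 1 is not shown. A remedy can refer only to the visits at which it is in fact collected.

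**The case against.** The case on the other side has real weight.

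- A reader might infer that psychiatric harm, or anything after session 10, cannot reach the safety conclusion at all. The article does not support that. The serious-event route is limited by neither type nor time, Blinding allows the code to be broken for a participant's safety, well-being is asked about before every session, and the team sees participants daily during the intervention. This stands and restricts the point to non-serious effects.
- A reader might treat the DISYPS III as an efficacy measure that is read only as a group mean. The article says neither. Its stated purpose is to detect change, no direction is given for comorbid symptoms, and no analysis of it is described. An invented example, nine participants improving by 0.3 SD and one worsening by 2 SD, gives a mean of (9 × −0.3 + 2.0)/10 = −0.07 SD. That shows how a mean can hide one case, but it is not evidence about this plan.
- The Discussion's phrase "having only mild and transient side effects" might look like a conclusion planned for this trial. It carries citations and describes existing literature, so it is not part of the case.
- The stated goals contain no safety objective, and the Discussion frames the questionnaire around mild effects of stimulation. This lowers the stakes. It does not remove them, because the Abstract announces a finding on tolerability without that limit.
- A condensed article may leave adverse-event recording to the full protocol. That is fair for recording procedures. However, the article does state the instrument, its timepoint and the status of the DISYPS III, and the point concerns those stated choices. If open recording through follow-up exists in the full protocol, saying so would settle much of it.
- The items of the sensations questionnaire are not reproduced. Its scope is taken from its title.

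**Conclusion.** The point holds in a limited form. As written, the tolerability assessment consists of one sensations questionnaire at the final session, and the DISYPS III has no safety role. Non-serious worsening of depression, anxiety or aggression, and non-serious effects over the roughly 26 weeks from session 10 to the 6-month visit, are not prespecified as part of it. Serious events are covered. Exclusion after such an event may, however, also end that participant's later ratings.

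This is a cheap improvement rather than a flaw that undermines the trial. It rests on three assumptions: that the questionnaire's content matches its title, that the full protocol adds no open recording of adverse effects, and, for the percentages only, that the arms have 10 participants each.

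**What to change.** At each visit where the DISYPS III is collected, treat its depression, anxiety and conduct/aggression ratings as descriptive safety data in addition to their exploratory role. Fix in advance how much worsening from a participant's own baseline counts. List the participants who reach it by arm, and give the proportion per arm with an exact confidence interval. At the post, 1-month and 6-month visits, ask one open question on new or worsened symptoms, in the same words in both arms, and tabulate the answers by arm.

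If this is not done, state in the report that the tolerability conclusion is limited to stimulation sensations at the final session.

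The cost is a few minutes per visit and one listing, with no new instrument and no extra visit. Some natural fluctuation will be listed as worsening, for which the sham arm is the reference. With about 10 per arm, no formal comparison should be attached to the listing.
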